##### **d. Societal Perspective**

It includes all the costs borne by ACF and its partners, the health system and beneficiary households.

##### **e.Efficacy data**

The cure rate among all children enrolled in the study, and per arm, will be the main outcome of interest for the economic evaluation. We will explore the cure rate per arm at the end of the 12 weeks maximum treatment, and also we will be able to evaluate the cure rate including the children referred to UNTI who return to UNTA and positively complete their treatment.

##### **f. Costs included**

The costs included will relate to prospective costs that may modify the result, i.e. cost of the treated child including the costs of outpatient and inpatient treatment for children who will have complications:

- Direct medical costs (consultation costs for treatment, including drugs, exams, staff time, outreach activities, etc.)
- Direct non-medical costs (implementation time for staff, costs payable by beneficiaries),
- Indirect costs (loss of productivity of beneficiaries corresponding to the time spent receiving the consultation).

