The nutritional treatment of severe acute malnutrition consists essentially of the administration of ready-to-use therapeutic foods (RUTF). For children who suffer from SAM without complications, the management is done on an outpatient basis with RUTF, a peanut paste enriched with powdered milk, vegetable oils, sugars, vitamins and minerals.(13) (14), according to the strategy of integrated management of acute malnutrition (PCIMA) unlike previous protocols where children were treated with F75 and F100 milks in a hospital environment (15) (16) (14).

A series of bottleneck analyzes (17)carried out in the West and Central Africa region in 2018 documented key issues regarding the delivery and uptake of outpatient SAM care. Major issues include lack of trained human resources, support costs, long waiting times, stockouts and geographic access. RUTF stock-outs are one of the obstacles to accessing and participating in the PCIMA program. These ruptures would be due to the large volume and the difficulties encountered in the transport of RUTF(18). In the DRC, for example, only 15 to 20% of children suffering from acute malnutrition, i.e. 495,000 to 660,000, could have access to acute malnutrition treatment services.(19). Because all of the countries (73 in total) that benefit from the PCIMA program are totally dependent on UNICEF or the Clinton Foundation, it is difficult

to ensure the sustainability of the PCIMA. The high cost of RUTF (around 50% of the total cost of PCIMA), would prevent respective governments from ensuring their own supply(20).

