##### b. Additional results

The additional results expected in this study, in the two groups (control and intervention), are:

- **The duration of the edema melting:** calculated in number of days, this indicator corresponds to the time taken for the lower limbs of SAM children to return to their normal volume. The expected result is the onset of melting of the edemas within the first 14 days after admission and their complete disappearance after 21 days of treatment.
- **The length of stay:** calculated in number of days, this indicator corresponds to the time elapsed between admission and discharge ( $PB \geq 12.5\text{cm}$  and / or  $PT \geq -3$  Z score and / or edema melt). The maximum length of stay is 12 weeks or 3 months(12).
- **The cure rate:** A child will be considered cured if he meets the cure criteria according to his admission category: A  $PT \text{ index} \geq -1.5$  or  $PB \geq 125 \text{ mm}$  during two consecutive visits and no edema during two visits (2 consecutive weeks).
- **The dropout rate:** it is the proportion of children confirmed alive who missed two successive visits. The abandonment is confirmed once after the visit of the RECO which confirms that the child is alive despite his 2 absences during the weekly visits. Children who have abandoned will be followed up to 3 months after the abandonment. For children who can be found, offer the caregivers a small snack at the single appointment 3 months after abandonment to take the anthropometric measurements.
- **Death rate :** the proportion of children randomized to the study who died during the intervention at any time.
- **Cost savings** (average cost saved and cost saved per child treated): this involves comparing the cost of treatment for children in care and declared cured in the two groups. We will use a societal perspective including the direct costs of drugs and RUTF

(purchase, transport, transport and storage) to assess the cost for each child, the HR costs involved in the care, the non-medical costs (food and transport. beneficiaries), indirect costs (loss of productivity).

- The growth velocity of the anthropometric variables and indices: it will be a question of evaluating the prevalence of stunting, underweight of the children included in the study in the two groups at the end of the treatment.

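### The costing annex values household productivity loss only for consultation time, which is narrower than its own societal perspective and leaves caregiver travel, waiting and inpatient accompaniment time unvalued

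*Protocol*

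**What the plan says.** The protocol describes household costs in three places.

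- Annex 5, 3.1 d (Societal Perspective): "It includes all the costs borne by ACF and its partners, the health system and beneficiary households".
- Section 2.1.4 b (Additional results, cost savings) lists "the HR costs involved in the care, the non-medical costs (food and transport. beneficiaries), indirect costs (loss of productivity". Productivity loss carries no restriction here.
- Annex 5, 3.1 f (Costs included): "Indirect costs (loss of productivity of beneficiaries corresponding to the time spent receiving the consultation". This is the operative cost list, and it is the only place that restricts productivity loss.

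The scope in 3.1 f also covers "cost of the treated child including the costs of outpatient and inpatient treatment for children who will have complications". The exclusions in 3.1 g are research costs, existing infrastructure and the sponsor's support costs; caregiver time is not among them.

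Staff time appears twice in 3.1 f. One entry is "Direct medical costs (consultation costs for treatment, including drugs, exams, staff time, outreach activities, etc" and the other is "Direct non-medical costs (implementation time for staff, costs payable by beneficiaries". Nothing says how they differ.

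**The concern.** A societal analysis should price the time that families give up. Here the declared perspective is wide and the counting rule is narrow, and an analyst following 3.1 f would price only the minutes with the provider. Section 1.1, reporting on outpatient care in West and Central Africa, says: "Major issues include lack of trained human resources, support costs, long waiting times, stockouts and geographic access". The protocol therefore recognises waiting and access as burdens, but its cost rule does not value the time they take. A caregiver's days at the UNTI are not consultation time on any ordinary reading, yet inpatient treatment is within the costing.

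This time grows with each weekly visit and each inpatient day. Length of stay and transfer to hospital are themselves secondary outcomes (section 1.2). Under Annex 5, 3.1 c, a finding of non-inferiority leads to a cost-minimization analysis, in which cost is all that is compared. Its result is a percentage of total cost (3.1 i), and Annex 8 also lists a percentage saving, so even an omission that is equal in both arms moves a stated result.

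**Working it through.** The protocol gives no unit cost, wage, travel time or waiting time for this trial, so there is no planned figure to reproduce. The calculation below shows scale only.

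**Inputs from the protocol (Annex 5, section 1):** an earlier evaluation found $91 per child on the standard dose and $75 on the reduced dose, with a mean stay of 8 weeks in both arms. The annex does not say which household time those figures contain; I treat them as excluding the time at issue.

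**Assumptions (not in the protocol):** one visit per week, so 8 visits; 0.5 h of consultation per visit; 2-4 h of travel and waiting per visit; time worth $0.25-0.50 per hour; an inpatient stay of 7-10 days at 8 h per day.

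**Base.** Saving = 91 - 75 = $16, and 16/91 = 17.6%.

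**Time counted and omitted per child**
- Counted: 8 × 0.5 × 0.25 = $1 to 8 × 0.5 × 0.50 = $2.
- Omitted: 8 × 2 × 0.25 = $4 to 8 × 4 × 0.50 = $16, that is $0.50 to $2 per visit.
- Share of visit time captured: 0.5/2.5 = 20% to 0.5/4.5 = 11%.

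**Effect on the saving.** With omitted time X added to both arms, the percentage is 16/(91 + X). If the reduced-dose arm makes k extra visits, each with omitted time worth v, the saving is 16 - kv. Only the omitted time of the extra visits is added; their other costs are held out.

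| v per visit | X (8 visits) | Equal visits | 1 extra visit | 2 extra visits |
|---|---|---|---|---|
| $0.50 | $4 | 16/95 = 16.8% | 15.50/95 = 16.3% | 15/95 = 15.8% |
| $2.00 | $16 | 16/107 = 15.0% | 14/107 = 13.1% | 12/107 = 11.2% |

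With equal visits the $16 stands and the percentage falls by about 0.7 to 2.6 points. With unequal visits the dollar difference moves as well.

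**Inpatient accompaniment.** Per stay: 7 × 8 × 0.25 = $14 to 10 × 8 × 0.50 = $40. This applies only to transferred children. At an assumed transfer rate of 5-10% it averages 0.05 × 14 = $0.70 to 0.10 × 40 = $4 per enrolled child. Each 5 percentage points by which transfers differ between arms would move the difference by 0.05 × 14 = $0.70 to 0.05 × 40 = $2.

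**Staff time, if some hours were duplicated.** With an assumed $5-20 per child counted twice in both arms, removing the duplicate leaves $16 and gives 16/86 = 18.6% to 16/71 = 22.5%. Duplication would understate the percentage, the opposite direction from the omitted time.

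**The case against.** Several points on the other side stand.

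- **Travel is not free in the plan.** Section 2.1.4 b counts "the non-medical costs (food and transport. beneficiaries), indirect costs (loss of productivity", and 3.1 f includes costs payable by beneficiaries. A reader might infer that travel and hospital stays cost nothing. The documents do not support that: transport money and inpatient treatment are counted, and only caregiver time is left out.
- **Extra visits are not priced at zero.** Annex 5, 3.2.2 adjusts for the visits actually made in each arm, so an extra visit brings its consultation time and out-of-pocket cost.
- **Staff are not shown to be added twice.** A reader might infer this from the two entries, but they are worded differently and may cover different hours. Annex 5, 3.2.2 also reports human resources as one expenditure item, where a duplication could be noticed. What stands is an undefined boundary, and hence a risk.
- **The wording may be a translation artefact.** The text reads as a rough translation, and the phrase may have meant time spent obtaining the consultation. That could rescue travel and waiting but hardly a stay at the UNTI, and it is a reason to settle the wording before data are collected.
- **The assumed hours may be high.** Section 2.1.1 calls geographic access relatively good, and section 2.1.5 makes it a criterion for choosing sites. This affects the size of the effect and leaves the inconsistency in place.
- **Equal stay is hypothesised, and the earlier evaluation found it.** That protects the dollar difference, but it is a hypothesis under test. Transfer to hospital is not among the indicators that the secondary hypotheses list as equal.

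It could also be said that time valuation belongs in a later costing plan. That would answer a silence, but 3.1 f states a rule, and the rule conflicts with 3.1 d and 2.1.4 b.

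**Conclusion.** The inconsistency is real and its effect is modest. Read literally, 3.1 f leaves caregiver time for travel, waiting and accompanying a child at the UNTI unvalued, against a perspective that claims all household costs. If that time is equal in both arms, the absolute saving is unaffected and the percentage saving is overstated: 17.6% against 15.0-16.8% in the illustration. If visits, stay or transfers differ by arm, the absolute difference is biased too, in a direction that depends on which arm has more. These sizes rest on assumed hours and wages and on an earlier evaluation's costs.

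A reader might conclude that the trial's societal saving will be wrong. The documents do not show that: they contain no cost for this trial, and no difference between arms in visits, stay or transfers is established. The primary endpoint and sample size are untouched. The point still deserves correction, because it concerns a stated secondary result and Annex 5, 3.2.1 c places cost collection during enrolment, after which unrecorded time is hard to recover.

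**What to change.** In Annex 5, 3.1 f, define indirect costs as caregiver time lost to travel, waiting, consultation and days accompanying the child at the UNTI, in line with 3.1 d and section 2.1.4 b. Add questions on travel time, waiting time and inpatient days to the caregiver interviews already planned in Annex 5, 3.2.1 a, before cost collection begins.

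As a secondary clarification, state which hours each of the two staff-time entries covers, so that every staff hour is counted once. Do not simply delete the second entry: if it describes a separate activity, deletion would remove a real provider cost from an analysis that claims to include the health system.

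The cost is a short edit to one list and slightly longer interviews. No extra staff or visits are needed.

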#### **g.Excluded costs**

Excluded costs (which do not change the result, for example the cost of the child treated):

- Research costs (researchers, team supervisors, research training)
- Costs of existing infrastructure (buildings, water, electricity, latrines, etc.)
- Support costs by ACF (ACF offices, ACF staff in DRC and Paris).

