### **3.6. Declaration of interests**

The investigators reassured that they had no conflict of interest in carrying out this study despite the fact that the principal investigator was also a technical expert in nutrition with PRONANUT, an organ of the Ministry of Health dedicated to nutrition. The participation of donors is excluded. The participation of the study sponsor (ACF) in the study is strong due to its dual role of co-investigator as well as sponsor.

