#### **2.2.Specific objectives**

The specific objectives of this study are:

- Estimate the costs from a societal point of view, including the costs borne not only by ACF and its partners but also by the beneficiaries of SAM treatment.
- Estimate the cost of SAM treatment for a child, with standard dose and with reduced dose
- Estimate the impact of a reduced dose on costs, taking into account its impact on efficacy results.

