#### **i. Expected results**

- a. Average cost per SAM child treated for a child on standard dose and on reduced dose
- b. If a Cost Minimization Analysis then we will obtain a percentage of the total cost of treatment under reduced dose compared to that of children in the control group;
- c. If a Cost Effectiveness Analysis then we will obtain a cost ratio per additional SAM child cured by the reduced dose approach

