| Evaluate the duration of treatment for each participant in the two groups                    | Duration of the treatment                    | Time between admission and discharge (PB≥12.5cm or PT ≥-3 Z score or edema melt)                                                                                                         | number of days           | interval |
| Assess dropout, cure, treatment failure and mortality rates                                  | Dropout rate in each arm                     | Number of children who have abandoned treatment and who no longer come to the center even after 3 home visits / total of children followed in each arm                                   | percentage               | interval |
|                                                                                              | Recovery rate                                | Percentage of children having reached the discharge after 3 months of treatment                                                                                                          | percentage               | interval |
|                                                                                              | Proportion Transfer to hospital in each arm  | Number of children being transferred to hospital during treatment (3 months) following a medical complication or if stagnation or loss of appetite / total children followed in each arm | percentage               | interval |
|                                                                                              | Proportion of Deaths in each arm             | Number of children who died during the stay at UNTA or during transfer to UNTI / total child followed in each arm                                                                        | percentage               | interval |
| Evaluate the cost and savings made with a reduced dose of RUTF compared to the standard dose | % savings in SAM treatment with reduced dose | Difference in cost between treatment with standard dose and treatment with reduced dose, expressed in%                                                                                   | percentage               | interval |

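### Annex 5 promises a full societal cost but excludes sponsor support and existing infrastructure, for a reason that fails for the average cost per child and the percentage saving

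*Protocol*

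**What the plan says.** **Perspective.** Annex 5, 3.1 d (Societal Perspective) says: "It includes all the costs borne by ACF and its partners, the health system and beneficiary households". The specific objectives in Annex 5, 2.2 also ask for societal costs, "including the costs borne not only by ACF and its partners" but those of beneficiaries too. Section 3.6 of the protocol confirms that ACF is the sponsor, with a "dual role of co-investigator as well as sponsor".

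**Exclusions.** Annex 5, 3.1 g opens with its reason: "Excluded costs (which do not change the result, for example the cost of the child treated"). Besides research costs, the list has two items: "Costs of existing infrastructure (buildings, water, electricity, latrines, etc.") and "Support costs by ACF (ACF offices, ACF staff in DRC and Paris").

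**Planned outputs.** Annex 5, 3.1 i gives:
- (a) "Average cost per SAM child treated for a child on standard dose and on reduced dose";
- (b) under a cost-minimization analysis, the reduced-dose treatment cost as a percentage of the control cost;
- (c) under a cost-effectiveness analysis, a cost ratio per additional child cured.

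Annex 5, 3.1 c makes (b) the result if non-inferiority is shown and (c) the result otherwise. Annex 8 adds a percentage saving, defined as "Difference in cost between treatment with standard dose and treatment with reduced dose, expressed in" per cent. In the main body, section 2.1.4 b defines the cost outcome as an average cost saved and a cost saved per child treated.

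**The concern.** The perspective says all costs, and the exclusion list takes some of them out again. Sponsor offices and staff are costs borne by the sponsor. Existing infrastructure falls at least partly on the health system. Both groups are named in the perspective.

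The reason given for the exclusion is also wrong for part of what will be reported. It names the cost per treated child as something the exclusions leave unchanged, yet that cost is output (a). Two further outputs are percentages whose denominator is a cost level.

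At stake is how the economic figures may be read. An average that leaves out shared costs is too low to be presented as a societal cost per child. A percentage saving computed on a smaller denominator is larger than the one the declared perspective would give. If the trial succeeds, the result that Annex 5 prescribes is this kind of percentage.

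**Working it through.** The protocol states no cost per child and no percentage saving for this trial, so there is no figure of its own to reproduce. The check is algebra, illustrated with the two costs cited in Annex 5, section 1.

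**Inputs**
- Cited earlier study: S = 91 dollars per child on the standard dose and R = 75 dollars on the reduced dose, with a mean stay of 8 weeks in both arms.
- The secondary hypotheses expect the same length of stay in both arms and a lower cost with the reduced dose.
- c = omitted cost per child, taken as equal in both arms. This is assumed; the protocol gives no value or bound.

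**What happens to each output when c is added back**

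| Output | Without c | With c | Changed? |
|---|---|---|---|
| Absolute saving (2.1.4 b) | S − R | (S + c) − (R + c) = S − R | No |
| Incremental ratio (3.1 i c) | (R − S) / difference in cure | same numerator | No |
| Average cost per child (3.1 i a) | S, R | S + c, R + c | Yes, by c in each arm |
| Cost as % of control (3.1 i b) | R / S | (R + c) / (S + c) | Yes, rises if R < S |
| % saving (Annex 8) | (S − R) / S | (S − R) / (S + c) | Yes, falls if R < S |

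The total cost per arm in Annex 5, 3.2.2 is also a level, and changes in the same way as the average.

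**Numbers, for illustration only**

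| c (assumed, dollars) | R + c | S + c | Absolute saving | Cost as % of control | % saving |
|---|---|---|---|---|---|
| 0 | 75 | 91 | 16 | 82.4 | 16/91 = 17.6 |
| 10 | 85 | 101 | 16 | 84.2 | 16/101 = 15.8 |
| 30 | 105 | 121 | 16 | 86.8 | 16/121 = 13.2 |
| 50 | 125 | 141 | 16 | 88.7 | 16/141 = 11.3 |

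**If the omitted cost differs by arm.** Write it as cR and cS. The reported saving is too high when (R + cR)/(S + cS) > R/S, that is when cR/cS > R/S = 75/91 = 0.824. The direction would reverse only if a reduced-dose child used less than 82.4% of the support and infrastructure cost of a standard-dose child. For example, with cS = 50 and cR = 37.5, the full saving is 1 − 112.5/141 = 20.2%, above 17.6%. Nothing in the protocol suggests such a gap. With unequal omitted costs the absolute saving would also move, by cS − cR.

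**The case against.** **The exclusion can be read as openly declared incremental costing.** Section 3.1 f counts costs that may modify the result, 3.1 g lists what is left out, and only the RUTF dose differs between the arms. For a difference in cost this is sound. It does not cover an average or a percentage, and nothing in Annex 5 limits the perspective to incremental costs.

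**The main-body outcome is already an absolute saving.** Section 2.1.4 b defines it so, and equal omitted costs leave it unchanged. This stands. A reader might infer from the exclusion that the saving itself is overstated, or that the percentage is the trial's main economic result. The protocol supports neither: the percentages appear only in Annexes 5 and 8, and the one in 3.1 i applies only under cost minimization.

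**Sponsor-funded delivery is not removed wholesale.** RUTF, drugs and staff time for care remain counted in section 2.1.4 b and in Annex 5, 3.1 f and 3.2.2. This also stands: the exclusion concerns offices, sponsor staff and existing infrastructure.

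**Part of the excluded staff time is research.** Sponsor staff sit on the steering committee and coordinate the study, and leaving research costs out is not in dispute. So not all of the excluded sum is missing societal cost.

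**The size is not evidence.** The amounts of 10, 30 and 50 dollars are assumptions. The protocol also does not say whether the cited 91 and 75 dollars already contain overhead; if they do, adding c would count it twice. This stands, and the figures show only the mechanism.

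**Conclusion.** The stated perspective and the exclusion list contradict each other, and the reason given for the exclusions is false for three planned outputs: the average cost per child, the reduced-dose cost as a percentage of control, and the percentage saving. On the protocol's own premises, a cheaper reduced dose and about equal omitted costs per child, the averages are too low for a societal label and the percentage saving is too high.

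The size cannot be stated. A reader might infer that the saving is overstated by a third, since 30 dollars of omitted cost gives 121/91 = 1.33. That factor comes entirely from choosing 30 dollars, and no figure in the protocol supports the choice.

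The absolute saving and the incremental ratio are unaffected as long as the omitted costs are equal between arms. The primary endpoint is not touched. The point is worth correcting because it decides how a secondary objective's figures may be described, and the correction is small.

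**What to change.** 1. In Annex 5, 2.2 and 3.1 d, restate the perspective as limited to the costs listed in 3.1 f and subject to the exclusions in 3.1 g.
2. In 3.1 g, delete the claim that the exclusions leave the cost per treated child unchanged. Say instead that they are omitted because they are expected to be equal per child in both arms, so that the absolute difference does not depend on them.
3. Report the absolute saving per child, already foreseen in section 2.1.4 b, as the lead cost result.
4. Label the averages and percentages in 3.1 i (a), 3.1 i (b) and the Annex 8 row as *of the included costs*. The total cost per arm in 3.2.2 needs the same label.
5. Optional: a sensitivity analysis that adds sponsor programme support costs, without research costs, to both arms. Requiring sponsor overhead and infrastructure to be allocated per child in the main analysis would be a debatable choice of scope, and the protocol does not show that it would be cheap.

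The first four items are wording only. The price is that the averages and percentages carry a narrower label and can no longer be presented as full societal costs.
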